### Secondary outcome measures

Secondary outcome measures will be used to select the preferred method if there is no difference in the primary outcome at conclusion of the study. Secondary outcome measures include:The separate incidence of preoperative cholangitis;The number of drainage procedures required to achieve technical success;The proportion of patients with therapeutic success at 7 days after technical success;The total number of drainage procedures that involved (attempted) stent (re-) placement;The proportion of patients requiring crossover treatment;Interval bilirubin decrease at 7 days and 14 days after biliary drainage relative to the bilirubin level at randomization;The number of patients with rescheduled or cancelled laparotomy due to severe drainage-related complications;Quality of life, measured with the EORTC Quality of Life Questionnaire C-30 (QLQ-C30) and its biliary cancer module (QLQ-BIL21);Postoperative morbidity and mortality, as defined in Table 3, among patients who underwent combined extrahepatic bile duct and major liver resection. The International Study Group of Liver Surgery (ISGLS) definitions for post-hepatectomy liver failure, bile leakage and hemorrhage are used [14-16].

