### Data collection and monitoring

All preoperative and postoperative complications will be monitored. Patients complete questionnaires (QLQ-C30/BIL21) at the day of randomization, and at 7 days, 28 days, and 90 days after randomization. There will be regular contact between the trial coordinator and the participating centers. Baseline and outcome data are collected by designated data managers using a standardized case record form [see Additional file 2], which is monitored by the trial coordinator.

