#### Sample size

Determination of the sample size is split in a provisional and definitive calculation, because only little retrospective evidence is currently available for power estimation. A previous study from the primary study center showed a severe complication rate of 60% in the EBD group versus 18% in the PTBD group. In the DRAINAGE trial, a complication rate of 50% is expected after EBD and 25% after PTBD (i.e. a relative decrease of 50%). This estimation was further expanded with proportions for the number of complications, as shown in Table 4. Accounting for a 3% dropout, 53 patients are needed in each arm resulting in a provisional required sample size of 106 patients (Wilcoxon/Mann–Whitney rank-sum test for ordered categories; α = 0.95; β = 0.8).

**Table 4 Tab4:** **The estimated number of complications in each study group used to calculate the provisional sample size**

	EBD	PTBD
0 complications	50%	75%
1 complication	25%	17%
≥2 complications	25%	8%
Total proportion	100%	100%

The estimated proportion of patients is presented for each categorical number of complications.

Interim analysis after inclusion of 53 patients (50%) will provide the definitive sample size, which will be calculated based on the observed number of complications in the EBD group. The definitive sample size will be determined similar to the provisional sample size, again using a relative decrease of 50% in the proportion of complications unless the absolute decrease drops below 20%, which is defined as the lowest absolute decrease with clinical relevance.

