#### Data analysis

The principal analysis consists of an intention-to-treat comparison of the number of preoperative severe drainage-related complications. The research hypothesis will be evaluated using a Wilcoxon/Mann–Whitney rank-sum test with a two-sided 0.05 significance level. The comparison will be expressed in terms of a relative risk and 95% confidence intervals, as determined with multinomial logistic regression.

Subsequent analyses are directed at the secondary endpoints. Continuous data will be presented as the mean with standard deviation or median with interquartile range depending on data distribution, and accordingly evaluated with Mann–Whitney U or t-test statistics. Categorical variables will be evaluated using Pearson’s chi-squared test or Fisher’s Exact test as applicable.

Preplanned subgroup analyses will be based on a dichotomized complication rate to retain statistical power (no complication versus 1 or more complications), and the analyses will consist of logistic regression with the subgroup and randomized treatment added as an interaction term. Subgroup analysis will be performed for patients with Bismuth type 4 tumors, and patients with a left-sided FLR.

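### Quality of life is measured at randomization, but the only test named for continuous secondary endpoints makes no use of that baseline score: valid, but less efficient than the collected data allow

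*Protocol article*

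**What the plan says.** All references are to the protocol article.

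- **Secondary outcome measures** lists "Quality of life, measured with the EORTC Quality of Life Questionnaire C-30 (QLQ-C30) and its biliary cancer module (QLQ-BIL21") among the secondary endpoints. It singles out no scale, visit or change score. The same section gives these endpoints a decision role: "Secondary outcome measures will be used to select the preferred method if there is no difference in the primary outcome".
- **Data collection and monitoring** fixes the timing: "Patients complete questionnaires (QLQ-C30/BIL21) at the day of randomization, and at 7 days, 28 days, and 90 days after randomization". Each patient therefore has a baseline score and up to three later scores.
- **Data analysis** has one sentence for continuous secondary data. They are summarised as mean and SD or median and IQR and "accordingly evaluated with Mann–Whitney U or t-test statistics". No baseline covariate, change score or longitudinal model is named, and no test specific to quality of life.
- For bilirubin, by contrast, the endpoint itself is defined "relative to the bilirubin level at randomization". Quality of life has no such definition.
- **Sample size** powers the primary complication count only. It gives no effect size, SD, correlation or power for quality of life.

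**The concern.** A patient's score before drainage usually predicts part of that patient's score afterwards. An unadjusted two-sample test leaves that predictable part in the error term, so the interval for the arm difference is wider than it need be. It also lets a chance baseline difference between arms pass into the apparent treatment effect.

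This matters more than usual for a secondary endpoint. Quality of life is part of the stated study aim, and secondary outcomes are to choose between the two drainage methods if the primary outcome does not separate them. The trial is small and was sized for a different outcome, so precision on quality of life is scarce. The baseline form is already being collected.

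**Working it through.** **1. The plan's own figure.** The article needs 53 per arm after allowing for 3% dropout, with the specification printed as "rank-sum test for ordered categories; α = 0.95; β = 0.8", which reads as two-sided 5% and 80% power. Simulating the tie-corrected rank-sum test on the Table 4 proportions (50/25/25% against 75/17/8%) gives power 0.80 at 51 per arm, and 51/0.97 = 52.6, rounded up to 53. The primary calculation is reproduced. It uses one count per patient, so the present point does not touch it.

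**2. Inputs for quality of life.**
- From the article: 53 per arm less 3%, about 51 analysable. This figure belongs to the primary outcome and is borrowed here.
- From the article: "two-sided 0.05 significance level", stated for the primary test and assumed here.
- Assumed: true difference d = 0.5 SD; equal SD at baseline and follow-up; baseline-to-follow-up correlation ρ from 0.3 to 0.7.

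**3. Formulas.** Power is taken from the non-central t distribution with non-centrality d*·√(n/2), where
- unadjusted follow-up score: d* = d
- change from baseline: d* = d/√(2(1−ρ))
- ANCOVA on baseline: d* = d/√(1−ρ²)

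For the unadjusted test the non-centrality is 0.5 × √(51/2) = 2.52.

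| ρ | Unadjusted t | Change score | ANCOVA | Gain, ANCOVA over unadjusted |
|---|---|---|---|---|
| 0.3 | 70.6% | 56.1% | 74.6% | 4 points |
| 0.5 | 70.6% | 70.6% | 82.3% | 12 points |
| 0.7 | 70.6% | 89.8% | 93.8% | 23 points |

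In simulation the Mann–Whitney test has 69–70% power in the same setting. The equivalent increase in sample size is 1/(1−ρ²): 1/0.91 = 1.10, 1/0.75 = 1.33 and 1/0.51 = 1.96.

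**4. Dependence on the reference point.** By normal approximation at ρ = 0.5:
- If ANCOVA has 80% power, the unadjusted test has 67.9%, a loss of 12.1 points.
- If the unadjusted test has 80%, ANCOVA has 89.9%, a gain of 9.9 points.
- At 53 per arm, effects of 0.3, 0.4, 0.5 and 0.6 SD give gaps of 9.1, 12.3, 11.4 and 7.6 points. The largest possible gap at this correlation is 12.4.

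**5. Chance baseline imbalance.** The baseline gap between arms has standard error √(2/51) = 0.198 SD. A gap above 0.3 SD is 0.3/0.198 = 1.51 standard errors, with two-sided probability about 13% under simple randomization. In simulations with no true effect, given such a gap, the unadjusted t-test rejects in about 8%, 12–13% and 22–23% of trials at ρ = 0.3, 0.5 and 0.7. ANCOVA stays at about 5%. Over all randomizations both hold 5%, because the unadjusted test rejects less often when the baseline gap is small.

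**The case against.** The strongest reply is that the sentence is a generic default in a journal article. It does not mention quality of life, does not say whether raw or change scores are tested, and does not exclude a longitudinal model in an analysis plan that is not shown. That stands in part: one cannot conclude that the baseline score will go unused. But the article does state a test for continuous secondary endpoints, and as stated that test is not adjusted for baseline. Reading change scores into it does not remove the point, since they are less efficient than adjustment at every correlation shown and no better than raw scores at 0.5.

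A reader might infer that the named test is wrong because the measurements are paired within patients. The article does not support that. The comparison is between two independent randomized arms, so a two-sample test has the right structure and keeps its 5% error rate. Pairing would decide the choice of test only for within-arm change, which is not planned.

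A reader might also infer that the trial loses 12 points of power. It does not: the article claims no power for quality of life. The 12 points need an assumed effect and an assumed correlation, and lie near the maximum for ρ = 0.5.

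Two further cautions hold. The 51 per arm presumes almost complete follow-up. That is doubtful for the day-90 form when the Background cites postoperative mortality of up to 18%, and the total of 106 is provisional. Also, the inflated error rates in step 5 apply only to the roughly 13% of trials with a large baseline gap. Minimization is on previous drainage, Bismuth type and center, not on baseline quality of life, so it does not directly prevent such a gap.

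**Conclusion.** The point holds as an efficiency improvement. For quality of life the article names a valid test that makes no use of an available baseline score. Under the assumptions of 0.5 SD, 51 per arm and correlation 0.3 to 0.7, adjustment would add about 4 to 23 points of power and would guard against chance baseline imbalance. The documents give neither the effect size nor the correlation, so the range is the result and no single value in it should be quoted as the trial's loss. The primary analysis and its sample size are not affected. Because secondary outcomes may decide the preferred method and the change is nearly free, it is worth making. Quality of life is, however, one of nine listed secondary outcomes, and no rule makes it decisive.

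**What to change.** In Data analysis, add a sentence for QLQ-C30 and QLQ-BIL21: the arms are compared with adjustment for the patient's score at randomization. Either of two forms will do:

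- ANCOVA at each of days 7, 28 and 90, with the baseline score as covariate; or
- one repeated-measures mixed model over the three visits, with arm, visit, arm-by-visit, baseline and baseline-by-visit terms and an unstructured within-patient covariance.

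Report the adjusted arm difference with its 95% confidence interval at each visit. A rank-based test can stay as a sensitivity analysis for skewed scales, which keeps the article's allowance for non-normal data.

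The cost is wording and slightly more modelling, with no extra patients, visits or forms. A rule for missing baseline forms is needed, such as mean imputation of the baseline score. Adjustment does not resolve scores missing because of death before day 90; that needs its own handling under any test. If an analysis plan already specifies such a model, the sentence in Data analysis only needs aligning with it.

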### Safety

An independent data safety monitoring board (DSMB), consisting of three independent specialists (surgeon, gastroenterologist, clinical epidemiologist) will evaluate the progress of the trial and examine the unblinded safety variables (serious adverse events, patients completing study follow-up) after 50% of inclusion (53 patients). The DSMB will assist and advise the principal investigators so as to protect the validity and credibility of the trial. Furthermore, annual unblinded safety reports, including all serious adverse events per group, are provided to the institutional review board.

## Discussion

Preoperative biliary drainage in PHC is a technically difficult procedure, associated with a high risk of severe drainage-related complications that may deteriorate the patients’ condition or increase the risk of postoperative morbidity and mortality after liver surgery. The majority of patients referred for surgical treatment have already undergone EBD procedures with attempted stent placement upon referral. However, preoperative EBD in PHC is associated with a high rate of complications: technical failures may occur because proximal tumors at the liver hilum are difficult to cannulate endoscopically; cholangitis may occur because isolated bile ducts with segmental obstruction may be left undrained after contrast injection; and pancreatitis may occur after repeated attempts at contrast injection. As an alternative, PTBD has a high rate of technical success because it offers selective segmental drainage, and it has a theoretically lower incidence of cholangitis because there is no retrograde bacterial contamination from the gut. Percutaneous drains also have the potential advantage of protecting hepaticojejunostomies from leaking postoperatively. Nonetheless, PTBD is associated with other drawbacks, including hemorrhage from perforated liver parenchyma, bile leakage, catheter dislocation, and patient discomfort. The DRAINAGE trial is designed to answer the question if preoperative PTBD is associated with fewer preoperative severe drainage-related complications compared to EBD.

Although PTBD is often in used in Western specialty centers, it has been associated with seeding metastases in 2-5% of patients after resection of PHC [12,19-21]. Consequently, most Eastern specialty centers chose to use preoperative endoscopic nasobiliary drainage (ENBD) as their preferred method, after its efficacy was consolidated in a large series of 164 patients [22]. Nonetheless, Western centers generally decline to use ENBD because it severely impairs patients’ quality of life. ENBD stents drain bile externally through a gastro-duodenal tube, and require bile suppletion either via the oral route or via a second gastro-duodenal tube. Moreover, an association with seeding metastases may not be limited to PTBD, as previous series have also shown seeding metastases after endoscopic drainage methods [23]. The DRAINAGE trial is designed to identify PTBD as the preferred preoperative drainage method despite the reported incidence of seeding metastases, because a negative effect of PTBD on survival after resection of PHC has insufficiently been shown.

The rarity of PHC complicates accrual of a sufficient number of patients in a randomized controlled trial. To overcome this challenge, all centers that specialize in surgical treatment of PHC in the Netherlands participate in the DRAINAGE trial, making it a nationwide study. The chosen “all-comers” design, which allows patients to be included in the study even if they underwent previous inadequate drainage procedures in regional centers before referral, will also improve the patient accrual. Moreover, this study design provides pragmatic results to answer the question how to treat any patient that presents with potentially resectable PHC and biliary obstruction in the future liver remnant.

## Abbreviations

PHC: Perihilar cholangiocarcinoma
EBD: Endoscopic biliary drainage
PTBD: Percutaneous transhepatic biliary drainage
FLR: Future liver remnant
MDT: Multidisciplinary team meeting
DSMB: Data safety monitoring board
